### Qualitative evaluation

An embedded qualitative research study will examine the intervention to explore mechanisms and components for subsequent testing. Ten PWPs and the trial occupational therapists will be interviewed. The participants will be asked if they want to take part in an interview at their final 24-week outcome measure session. If the participant wants to take part in an interview, a separate participant information sheet (PIS) for the qualitative interviews and a consent form will be provided. A provisional time and date for the interview will be set with the participant. The informed consent form will be completed with the participant immediately prior to the interview. The interview will be conducted online or on the telephone. Purposeful sampling will ensure the demographic representation of PWPs based on sex, location and baseline GAD-7 score.

The specific aims of this will be to investigate:

Acceptability of trial methods across both trial arms.Acceptability of the OBtAIN-PD.Impact that the OBtAIN-PD had on the lives of PWPs.Potential recruitment and retention barriers.Outcome measure suitability and burden.

### Sample size

The target sample size is 50. The number of PWPs in the site catchment areas is estimated as 1800 with 70% (1300) known to the Parkinson’s services. Around 50% are estimated to have anxiety (n=650).^52 53^ The presence of a severe cognitive impairment in Parkinson’s that is likely to impair mental capacity has an estimated point prevalence of 5%–10%.^54^,^56^ Assuming a retention rate of 80% at follow-up, this sample size would allow estimation of the overall retention rate with precision of ±11%. Assuming a non-differential follow-up rate of 80%, it is anticipated to follow-up a minimum of 20 participants in each of the two treatment groups, which would provide data to help inform indicative sample size calculations for a definitive RCT.

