### Study design

This is a pragmatic feasibility cluster randomised controlled trial (RCT), with assessor-blinded outcome assessment, cluster randomising community rehabilitation teams (CRTs) to implement either the OBtAIN-PD and usual occupational therapy care (intervention) or usual occupational therapy care alone (usual care). A cluster randomised design was chosen to help control for potential contamination between trial arms.^23^

Four CRTs across two sites (therefore, two CRTs at each site with one intervention and one usual care) will be allocated on a 1:1 basis to implement the OBtAIN-PD intervention plus usual care, or usual occupational therapy care alone, stratified by site with a block size of two. This will be logistically convenient and accommodate the current pressures on National Health Services while providing a control for contamination. Group allocation will be stratified by site.

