### Data collection, management and analysis

A web-based system developed by PenCTU will be used to electronically capture participant-level data and for general trial management. This consists of a bespoke online system for participant screening, consent, randomisation and management integrated with REDCap Cloud,^57^ which will capture electronic case report forms.

When registered on the data collection website, the OBtAIN-PD Research team will allocate each participant a unique trial number. PenCTU Data Management staff will monitor the completeness and quality of data recorded in the database and correspond regularly with the OBtAIN-PD research team to capture any missing data where possible and ensure continuous, high-quality data. All data will be collected and stored in accordance with the UK Data Protection Act 2018 and the General Data Protection Regulation 2018.

Reporting of the trial will be in accordance with the Consolidated Standards of Reporting Trials (CONSORT) guidance for pilot and feasibility studies and a detailed statistical analysis plan will be written and signed off prior to database lock. A CONSORT diagram will display data from screening, recruitment and follow-up logs and be used to generate estimates of eligibility, recruitment, consent and follow-up rates. Reasons for withdrawal will be reported where available. Completion rates will be estimated for outcome measures at each time point, including the health, social and wider care resource-use data. 95% CIs will accompany recruitment and retention rates to inform assumptions for planning the definitive trial. Adherence data will contribute to the evaluation of intervention acceptability and feasibility. As a feasibility trial, it is not powered to detect differences in outcomes between the groups—as such, no inferential statistical testing will be undertaken, and the analysis will be descriptive, using appropriate summary statistics and plots to illustrate any potential between-group differences.

The demographic and clinical characteristics of the sample at baseline will be summarised overall and by allocated group, using appropriate descriptive statistics (eg, means and SD for normally distributed data, numbers and percentages for categorical variables) to informally check for balance between the groups.

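### The ±11% retention precision assumes 50 independent participants, and the 'minimum' of 20 per group is an expected number under an equal split

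*Protocol article*

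**What the plan says.** The Sample size section gives a target ("The target sample size is 50") and attaches two numerical claims to it. The first is about precision: "Assuming a retention rate of 80% at follow-up", it states that "this sample size would allow estimation of the overall retention rate with precision of ±11" per cent. The second is about yield: "Assuming a non-differential follow-up rate of 80" per cent, "it is anticipated to follow-up a minimum of 20 participants in each of the two treatment groups", which is meant to supply data for indicative sample-size calculations. The section mentions no ICC, design effect or unequal group sizes, and does not say that independence is assumed.

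The Study design section describes the randomisation: "Four CRTs across two sites (therefore, two CRTs at each site with one intervention and one usual care) will be allocated on a 1:1 basis", "stratified by site with a block size of two". Under Study setting, each CRT serves its own geographical area. Under Recruitment, participants come through the usual clinical pathways, and no quota per team or arm is given. The analysis section (Data collection, management and analysis) gives the use of the result: "95% CIs will accompany recruitment and retention rates to inform assumptions for planning the definitive trial".

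**The concern.** The precision figure is what one would quote for a simple sample of 50 people. Here the 50 sit in four teams. From the numbers under Usual care and under the intervention description, each team has one trial therapist. If retention varies between teams more than chance allows, 50 people carry less information about the overall rate than 50 independent people would.

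The yield figure calls an average a minimum. It also presumes 25 people per arm, whereas the randomisation balances teams. An arm's size depends on how many people its two areas produce.

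What is at stake is limited to the feasibility estimates. The trial makes no inferential comparison, so no efficacy conclusion is affected. But supplying planning inputs is its stated purpose, and these are the only two precision or yield arguments offered for a target of 50. A reader planning the definitive trial could think retention better determined, and 20 per group more assured, than they are.

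**Working it through.** **Inputs from the protocol article.** Total n = 50, retention 0.80 in both groups, stated precision ±11% and stated yield 20 per group (Sample size). Four CRTs, two per arm (Study design), so the mean cluster size is 50/4 = 12.5. The Sample size section gives no confidence level; 95% is taken from the analysis section.

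**Assumption.** No ICC for retention is given, so a range of 0.01 to 0.10 is shown.

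**Step 1: reproduce ±11%.** Half-width = 1.96 × √(p(1−p)/n) = 1.96 × √(0.8 × 0.2/50) = 1.96 × 0.0566 = 0.1109. The figure reproduces, as an interval for independent participants. A Wilson interval (67.0% to 88.8%) or an exact interval (66.3% to 90.0%) makes the same assumption.

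**Step 2: allow for four teams.** Design effect DE = 1 + (12.5 − 1) × ICC. The half-width becomes 11.09% × √DE and the effective sample size 50/DE.

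| Assumed ICC | DE | Effective n | Half-width |
|---|---|---|---|
| 0 | 1.000 | 50 | ±11.1% |
| 0.01 | 1.115 | 44.8 | ±11.7% |
| 0.02 | 1.230 | 40.7 | ±12.3% |
| 0.05 | 1.575 | 31.7 | ±13.9% |
| 0.10 | 2.150 | 23.3 | ±16.3% |

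The result still rounds to 11% only if it is below 11.5%, that is, if DE < (0.115/1.96)²/(0.16/50) = 1.076. This requires an ICC below 0.076/11.5, or about 0.007. These rows take teams as equal in size. Unequal teams widen them a little: with a coefficient of variation of 0.5 and ICC 0.05, DE = 1 + (1.25 × 12.5 − 1) × 0.05 = 1.73, giving ±14.6%.

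**Step 3: reproduce 20 per group.** 50/2 × 0.8 = 20.0 exactly. This is the mean of a binomial count with n = 25 and p = 0.8.

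**Step 4: chance of reaching 20.** For 25 people at 80%, P(at least 20) = 0.617. For both groups it is 0.617² = 0.380. The 2.5th and 97.5th percentiles are 16 and 24. All of these take participants as independent.

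**Step 5: unequal arms, total still 50.**

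| Split | Expected followed up | P(both at least 20) |
|---|---|---|
| 25:25 | 20.0 and 20.0 | 0.38 |
| 26:24 | 20.8 and 19.2 | 0.34 |
| 28:22 | 22.4 and 17.6 | 0.14 |
| 30:20 | 24.0 and 16.0 | 0.01 |

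Because 0.8 × 25 is exactly 20, any unequal split puts the smaller arm's expected number below 20.

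**The case against.** The strongest reply is that nothing is miscalculated. Under independence ±11% is right, and the shortfall depends on an ICC that the protocol does not give; at 0.01 it is only 0.6 percentage points. Clustering may also be weak. Retention here means outcome follow-up, which one central blinded researcher conducts, remotely where possible, with a common reminder procedure. The therapists do not run it. This stands as a limit on size: clustering through treatment experience or locality is plausible, but its amount is unknown, and no single ICC should be presented as the true one.

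On the yield, the sentence is conditional on 80% follow-up and is framed as an expectation. The Recruitment section's workload estimate presumes similar numbers per therapist, and the strengths and limitations list concedes that clustering may unbalance the arms. All true, but the hedging does not turn a mean into a minimum, and a workload estimate is not a quota.

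A reader might infer several stronger things that the documents do not support.

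- **Much wider intervals from a t multiplier on 3 degrees of freedom.** At ICC 0.05 this gives about ±23%, an impossible upper limit of 103%. Most of the widening comes from the multiplier, which already gives ±18% at ICC 0.
- **About 17 per group, from the lower limit of 69%.** That applies an interval for the whole sample to one group.
- **That the retention interval will ignore clustering.** The article does not say so, and the method may be set in the analysis plan, which is not shown.
- **That the definitive trial will under-allow for dropout or trust a poor SD.** The definitive trial would use the observed interval, ±11% says nothing about an SD, and the article does not say which teams that trial will use.
- **That the whole case for 50 collapses.** The article also gives the size of the recruitment pool and the therapists' capacity.

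**Conclusion.** Two planning figures are worded more favourably than the design supports. The yield point is the firmer one, because it needs no outside assumption: 20 is the expected number at 25:25. At exactly 80% retention, with participants independent, both groups reach it with probability 0.38.

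The precision point is certain in direction for any positive ICC and uncertain in size. It runs from about ±11.7% to ±16.3% over assumed ICCs of 0.01 to 0.10, and at an ICC of zero ±11% is correct. Four teams are too few to settle the ICC from this trial's own data.

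Severity is minor to moderate. Neither point calls for a larger sample or a different design.

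**What to change.** Three changes, in the protocol wording, the analysis plan and the trial report:

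1. State that ±11% assumes independent participants, and add that with four CRTs of about 12.5 it would be about ±12% to ±16% for assumed ICCs of 0.01 to 0.10.
2. Replace the claim of a minimum with 'an expected 20 per group if recruitment is equal (95% range 16–24, taking participants as independent)'.
3. Report the retention interval allowing for clustering, with numbers recruited and followed up per CRT, so that whoever plans the definitive trial can see the spread between teams.

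The cost is wording and a small amount of reporting. The stated precision becomes slightly less favourable. A recruitment ceiling per CRT is not proposed: the Study setting section says that recruitment ended in October 2023, so the split between arms is already fixed.

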### Recruitment

Participants will be recruited through usual clinical pathways by staff unaware of allocation to reflect usual National Health Service practice as closely as possible while avoiding overwhelming the CRTs with an additional workload. Potential participants will be given an information pack by the clinician who has made contact. The information pack will contain an introductory letter, PIS, GAD-7 for screening purposes, a reply slip (including consent to contact form), a stamped addressed envelope, and the lead researcher’s telephone and email contact details. This information can also be emailed to participants at their request. The PIS and reply slip will encourage those who do not want to take part to return the reply slip stating their reasons for non-interest, but it will be emphasised that there is no obligation. This will provide valuable information for designing the main trial. Information packs sent out will be followed up by CRN research teams 1 week later via telephone to encourage responses.

Given the total sessions in the intervention and usual care group (eight sessions in 10 weeks), this recruitment rate results in an estimated 2–2.5 hours/week of occupational therapy per site for each occupational therapist dedicated to this project (n=2 per site). This reflects the current workload allocation (<5%) for PWPs for community occupational therapists.

### Allocation, concealment and blinding

Randomisation will be undertaken by the Peninsula Clinical Trials Unit (PenCTU, Plymouth, UK) to allow the lead researcher to remain blinded to group allocation. The CRTs will be provided with a unique, anonymous code. Within each site, the CRTs will be randomly allocated (1:1) into the usual care (60 min of usual occupational therapy management only per session) or intervention (30 min OBtAIN-PD plus 30 min of usual occupational therapy management per session). A statistician independent of the study generated the randomisation list. These will be sent to the coinvestigator (JM) who will inform the four CRTs of their treatment allocations. Recruitment will commence within 1–2 weeks of cluster allocation. Participants will then be booked, and treatment provided as per arm allocation. The randomisation list and the programme that generated it will be stored in a secure network location within the PenCTU, accessible only to those responsible for its provision. PenCTU staff, independent of the trial, will verify the integrity of the randomisation system throughout the trial according to established written protocols.

Access to the code/list will be confined to the PenCTU data programmer. No one else in the trial team will be aware of allocated trial arms until randomisation is completed, maintaining effective concealment. Following randomisation, only the individuals described above will be aware of the allocations to intervention or usual care arm; the blinded lead OBtAIN-PD researcher will NOT have access to treatment allocation.

Data will be collected on the following to aid in developing potential minimisation factors for a future definitive trial:

Time taken from referral to treatment.Access to specialist Parkinson’s rehabilitation services such as home-based care pathways and specialist Parkinson’s therapists.Organisation size.Size of population served.

The trial participants cannot be blinded in this trial due to the nature of the intervention they are receiving. Similarly, the National Health Service treating occupational therapists cannot be blinded. The occupational therapists will be aware of their allocation following the randomisation of their CRT. Participants will be aware of the treatment they receive from their first treatment session with the occupational therapist, such as through the receipt of OBtAIN-PD branded materials. The recruiting clinicians (consultants, Parkinson’s nurses, allied health professionals, and CRN research nurses) will not be informed of CRTs’ group allocation. The only exception will be the occupational therapists in the CRTs who will identify potential participants in their usual referral triage process.

The OBtAIN-PD lead researcher conducting all eligibility checks, screening assessments, consent and outcome assessments will be blinded to the participants’ allocated group until database lockdown, along with the team statistician. A second, unblinded statistician generated the group allocation script. Clinical outcomes will be taken remotely wherever possible, and participants will be asked to not reveal their geographic location or the treatment they have received to preserve assessor blinding. At each time point, all outcome measures are patient-reported assessments, thereby minimising the opportunity for the researcher to influence the outcome assessment. Every effort will be made throughout the trial to maintain blinding of the OBtAIN-PD lead researcher, for example, by reminding participants not to discuss their treatment with them.

Assessor blinding will be monitored and tested by recording ‘guess’ participation group allocation at each time point. The blinded OBtAIN-PD researcher will be asked to record on the electronic database any cases of inadvertent unblinding to group allocation at the end of the trial. If this occurs, they will be asked to explain how this unblinding happened. The research team (including the trial statistician) will finally be unblinded after the creation of a locked analysis data set and analysis has been undertaken.

### Data collection, management and analysis

A web-based system developed by PenCTU will be used to electronically capture participant-level data and for general trial management. This consists of a bespoke online system for participant screening, consent, randomisation and management integrated with REDCap Cloud,^57^ which will capture electronic case report forms.

When registered on the data collection website, the OBtAIN-PD Research team will allocate each participant a unique trial number. PenCTU Data Management staff will monitor the completeness and quality of data recorded in the database and correspond regularly with the OBtAIN-PD research team to capture any missing data where possible and ensure continuous, high-quality data. All data will be collected and stored in accordance with the UK Data Protection Act 2018 and the General Data Protection Regulation 2018.

Reporting of the trial will be in accordance with the Consolidated Standards of Reporting Trials (CONSORT) guidance for pilot and feasibility studies and a detailed statistical analysis plan will be written and signed off prior to database lock. A CONSORT diagram will display data from screening, recruitment and follow-up logs and be used to generate estimates of eligibility, recruitment, consent and follow-up rates. Reasons for withdrawal will be reported where available. Completion rates will be estimated for outcome measures at each time point, including the health, social and wider care resource-use data. 95% CIs will accompany recruitment and retention rates to inform assumptions for planning the definitive trial. Adherence data will contribute to the evaluation of intervention acceptability and feasibility. As a feasibility trial, it is not powered to detect differences in outcomes between the groups—as such, no inferential statistical testing will be undertaken, and the analysis will be descriptive, using appropriate summary statistics and plots to illustrate any potential between-group differences.

The demographic and clinical characteristics of the sample at baseline will be summarised overall and by allocated group, using appropriate descriptive statistics (eg, means and SD for normally distributed data, numbers and percentages for categorical variables) to informally check for balance between the groups.

The variables derived from participant reported outcomes will be calculated in accordance with published guidance. The amount of missing data will be summarised, but no imputation will be carried out unless in accordance with published guidance.

At each follow-up, all participant-reported outcomes will be summarised overall and by the allocated group with appropriate descriptive statistics. The change in these outcomes between baseline and follow-up will also be calculated and descriptive statistics for these reported overall and by allocated group, on an intention-to-treat basis. The between-group differences in change between baseline and follow-up will be reported with 95% CIs. Estimates of the correlation between baseline and follow-up outcome measures will be used to inform a future sample size calculation for a definitive RCT.

#### Qualitative evaluation

The qualitative data for analysis will include verbatim transcripts from the one-to-one interviews of participants and National Health Service occupational therapy staff. 10 purposively (using the Hoehn and Yar score) sampled participants from the trial will include five trial participants randomised to the usual care group and five participants from the intervention group. All trial occupational therapists will be offered an interview. These will be run through individual one-off semistructured interviews using an interview schedule (onlinesupplemental materials 1  2). The interviews will be conducted at the end of the trial period at a time, date and method (face-to-face or remote) convenient for the participant. Interviews will be recorded using a secure digital or web application (Microsoft Teams) to support transcription. The recordings will be securely deleted once the interviews have been transcribed and anonymised using pseudonyms. The anonymised transcribed data will be uploaded into NVivo V.12 software for organisation and analysis.^58^ Data will be analysed using thematic analysis adopting Braun and Clarke’s six-phase process of (1) data familiarisation; (2) generating initial codes; (3) searching for themes; (4) reviewing themes; (5) defining and naming themes and (6) writing up to identify patterns of meaning within the data sources.^59 60^ Two researchers will refine initial themes to maximise credibility and dependability. The occupational therapist interviews will be completed between December 2023 and March 2024. The participant interviews are scheduled to begin in April 2024.

Interviewees will be invited to review a draft of the analysis as part of a member-checking process to ensure their experiences are accurately represented.

#### Economic evaluation

The resources required to provide the intervention will be assessed, and a framework will be established for future cost-effectiveness analysis alongside a full RCT. Data on intervention resources will be collected via within-trial reporting, including participant-level contact and non-contact time and training for delivery staff. Participants will self-report health, social and wider care resource use using a resource use questionnaire adapted for this trial. Participants will complete the EQ-5D-5L (the anticipated primary economic outcome measure in a full trial) and assess the feasibility of estimating QALYs over the follow-up period. The economic evaluation methods will be developed to provide a future policy-relevant cost-effectiveness analysis of the intervention in the context of the UK National Health Service and Social Services.

